## Abstract

**Background:** Sleep disorders are one of the most frequent non-motor symptoms of Parkinson's disease (PD), and the efficacy of dopaminergic agents remains controversial. Clinical randomized control trials for the treatment of sleep disorders in PD are limited. Zonisamide (1,2-benzisoxazole-3-methanesulfonamide) improved motor symptoms and wearing-off in patients with PD. Patients with PD were reported to have dream-enacting behavior that was resolved after treatment with zonisamide. This study aimed to verify the safety and efficacy of zonisamide for sleep disorders and rapid eye movement (REM) sleep behavioral disorders using a mobile two-channel electroencephalography (EEG)/electrooculography (EOG) recording system.

**Methods and Analysis:** The present study is a randomized placebo-controlled trial to determine the efficacy of zonisamide for sleep disorders in patients with PD. This study was designed to be single-blind, but the subject allocation is randomized by an independent allocation manager via computer-generated block randomization. The subjects in the treatment group took zonisamide (25 mg per day) before bedtime for 28 days. The sleep index is analyzed using a portable EEG/EOG recording system collected on two consecutive nights within 7 days prior to the intervention and reobtained on one night within 2 days after the 28-day administration of zonisamide. The amount of change in sleep efficiency before and after the 28-day administration will be compared between the zonisamide treatment group and placebo group concerning the primary endpoint. As for the secondary endpoint, the change in the ratio of other sleep parameters, including REM sleep without atonia, or sleep architecture will be evaluated.

**Ethics and Dissemination:** The protocol was approved by the Nara Medical University Certified Review Board (CRB5200002). The trial was notified and registered with the Japan Registry of Clinical Trials (jRCTs051200160). Written informed consent will be obtained from every participant using informed consent approved by the CRB. The results of this trial will be disseminated through peer-reviewed scientific journals.

## Introduction

Sleep disorders are one of the most frequent non-motor symptoms of Parkinson's disease (PD), and the efficacy of dopaminergic agents remains controversial (1, 2). PD-related sleep disorders can be influenced by primary neuronal loss in the dopaminergic, cholinergic, serotoninergic, or other systems that are intrinsic to PD or secondary effects such as dopaminergic effects or from sleep medications (1, 3). The multifactorial conditions include nocturnal motor symptoms, psychosis, hallucinations, urinary incontinence, depression, cognitive impairment, vivid dreaming, or rapid eye movement (REM) sleep behavioral disorders (RBD), which elicit sleep fragmentation and difficulties in maintaining or falling asleep. Sleep fragmentation is the most common sleep disorder in PD, with an estimated rate of 74–88% (4, 5). Sleep fragmentation is closely associated with many burdens on PD pathology (6). Vivid dreaming and its elicited sleep behavioral disorders, so-called “RBD” can produce nighttime awakening, leading to an increase in sleep fragmentation. Since idiopathic RBD is recognized as the prodromal stage of neurodegenerative diseases, especially in PD globally (7), and PD with RBD has a faster progression and more cognitive decline (8, 9), RBD has been increasing in importance. RBD is also related to the degeneration of the brainstem sleep regulatory center. Thus, the association between insomnia and RBD has intensified (10). Sleep disorders are an early indicator of PD (7). Sleep disorders and excessive daytime sleepiness or unsteadiness, with a potential risk of falling, independently affect the quality of life in patients with PD.

Benzodiazepines or non-benzodiazepine receptor agonists are widely used treatments for insomnia in non-PD populations; however, these can cause side effects such as drowsiness, cognitive decline, and daytime unsteadiness. Sleep contributes to dopamine receptor regulation and dopamine storage, resulting in pathophysiological progression in PD (6, 11, 12). Clinical trials for the treatment of sleep disorders in PD are limited. Long-acting rotigotine showed significant improvement in difficulty in staying asleep, nocturnal motor symptoms including akinesia, and frequency of nocturia in 287 patients (placebo in 97 patients) (13). Chronic-release levodopa/carbidopa improved nocturnal akinesia and increased the total sleep time in 40 patients including placebo in 15 patients (14). The benefit of prolonged-release melatonin on sleep quality was seen in another study including 34 patients who received placebo in 18 patients (15). A placebo-controlled crossover study of melatonin (5 vs. 50 mg) in 40 patients showed a significant improvement in total nighttime sleep on actigraphy during the 50-mg melatonin treatment (16). Conversely, the patient's reported total sleep time on their diaries did not increase in one study that evaluated the efficacy of eszopiclone in 30 patients with polysomnographic-measured sleep impairment (placebo in 15 patients) (17). Actigraphic sleep efficiency and sleep fragmentation worsened in one study of pergolide in 22 patients, including placebo in 12 patients (18). A study evaluating the effect of doxepin and the non-pharmacologic combined treatment of cognitive-behavioral therapy and bright light therapy in 18 patients (placebo in six patients) reported no change in sleep outcomes in both groups on actigraphy (19). No significant difference was observed in the polysomnographic measures between eight patients receiving melatonin and 10 placebo patients (20). Overall, some medications have a benefit in subjective sleep measurement; however, the efficacy of sleep parameters is unlikely to be vague.

Zonisamide (1,2-benzisoxazole-3-methanesulfonamide) was launched in Japan and was effective for the treatment of PD in clinical trials (21–23). It improved motor symptoms and wearing-off in patients with PD, with a very low incidence of dyskinesia and psychiatric symptoms such as hallucinations (21–23). Its pharmacological mechanisms remain unclear, and the effect of zonisamide on non-motor symptoms was uncertain since the clinical trial has not been studied. More recently, an open-label study showed the efficacy of treatment with zonisamide on PD-specific questionaries in 20 patients with PD receiving 25 mg (60%) and 50 mg (40%) (24). Zonisamide has a long-half life with a low potential for interacting with other medications (25) and its effect may improve the nocturnal motor symptoms, leading to subsequent improvement in sleep disorder. Moreover, in 2012, a patient with PD was reported with vivid nightmares and dream-enacting behavior that was dramatically resolved after treatment with zonisamide (26). In 2015, Ikeda et al. evaluated the therapeutic effects of zonisamide monotherapy in 10 patients with *de novo* PD, and three patients with a prior history of RBD markedly inhibited nocturnal symptoms of RBD after zonisamide treatment (27). These findings raised an open question as to whether zonisamide might have some potential improvement in sleep disorders in patients with PD.

This study aims to verify the safety and efficacy of zonisamide not only for sleep disorders but also for RBD using a mobile two-channel electroencephalography (EEG)/electrooculography (EOG) recording system.

## Methods and Analysis

### Participants and Recruitment

The present study is a randomized placebo-controlled trial to determine the efficacy of zonisamide for sleep disorders in patients with PD. All procedures were conducted at the Nara Medical University Hospital in Japan. A total of 70 patients were diagnosed with PD according to the International Parkinson and Movement Disorder Society (MDS) diagnostic criteria (28); however, the decline in the striatal uptake on the dopamine transporter in single-photon emission CT does not matter. All patients ≥41 years during the informed consent procurement have at least one sleep problem among the three of the following items: (1) they answered “Sometimes (2–3 times a week),” “Almost none (once a week),” or “Nothing” on item 1 scored regarding “Did you sleep well last week?”; (2) answered “Sometimes (2–3 times a week),” “Many (4–5 times a week),” or “So much (6–7 times a week)” on another item 2 scored regarding “Did you have a bad day at night?” on the PD Sleep Scale (PDSS)-2 Japanese version (29); or (3) they have a score ≥5 on the 10-item no/yes Sleep Behavior Disorder Screening questionnaire Japanese version (RBDSQ) with a maximum score of 13 (30). The PDSS-2 consists of 15 questions regarding PD-related nocturnal symptoms, and it is widely used as a recommended, valid, and highly reliable scale and the validity and reliability of the Japanese version were established (29). RBDSQ provides greater sensitivity and reasonable specificity for RBD compared with polysomnography (31). A cut-off score of ≥5 points has been found to have high sensitivity, specificity, and reliability in the Japanese population (29). All patients have a Mini-Mental State Examination score of ≥22 to preclude the following instructions. All patients are outpatients with Hoehn and Yahr stages 1 to 4 and received oral levodopa before entry. The regimen and dosage of antiparkinsonian medication were stable for at least 2 weeks prior to clinical trial participation.

The exclusion criteria includes the following: patients who had been treated with zonisamide within 3 months prior to obtaining informed consent, with a history of brain surgery including deep brain stimulation surgery, a history of other organic cerebral disorders such as stroke and epilepsy, hepatic or severe renal dysfunction with estimated glomerular filtration rate <30, taking antiepileptic drugs, taking both monoamine oxidase-B (MAO-B) inhibitors and tricyclic antidepressants, severe dyskinesia, severe mental disease, with potential and intention to become pregnant, with a history of malignant syndrome, with suicide attempts, toxic epidermal necrolysis, mucocutaneous ocular syndrome (Stevens–Johnson syndrome) or erythroderma (exfoliative dermatitis), history of hypersensitivity syndrome, interstitial pneumonia, or rhabdomyolysis within 5 years prior to obtaining informed consent, aplastic anemia, agranulocytosis, pure red cell aplasia, or thrombocytopenia, with pacemakers, and a history of hypersensitivity to the components. The subjects who were eligible according to the inclusion criteria provided written consent for participation in this trial.

### Randomization and Blinding

The patients from the treatment and control groups were randomized in a 1:1 ratio (Figure 1). This study is designed to be single-blind, but the subject allocation was randomized by an independent allocation manager *via* computer-generated block randomization.

**Figure 1 F1:**
[figure not shown]
Flowchart of the study showing randomized control trials.

### Intervention

The subjects in the treatment group took zonisamide (25 mg per day) before bedtime for 28 days. If the dosage of the following medications is stable from 2 weeks before enrollment to the initiation of the intervention, both groups are allowed to receive conventional anti-PD medications including L dioxyphenylalanine (L-DOPA), dopamine agonists, catechol-*O*-methyl transferase inhibitors, monoamine oxidase (MAO) inhibitors, and other antiparkinsonian drugs other than zonisamide, tricyclic or tetracyclic antidepressants, antiepileptic agents, reserpine derivative, phenothiazines, butyrophenone drug, sulpiride, or metoclopramide. All these medications were prohibited from new dosing during the clinical trial period, and a constant dose of these medications was maintained during the intervention. The conventional treatment for comorbidity and complications, sleep stabilizers, or other medications related to PD, such as antidementia drugs, antipsychotics, anxiolytics, or selective serotonin uptake inhibitors, will be allowed, but these dosages will be stable during the clinical trial. Supportive care for maintaining PD status such as rehabilitation before the clinical trial participation's consent would be performed; however, surgery such as deep brain stimulation would not be tolerated. The criteria for discontinuing this clinical trial are withdrawal of the trial participation agreement by subjects or their legal representatives, violation of the selection/exclusion criteria, the occurrence of adverse events that make it difficult to continue the clinical trial, and <70% compliance with the medication criteria.

The schedule of the intervention and outcome measurements is shown in Figure 1.

To improve adherence to clinical trials, this clinical trial will be regulated to monitor patient safety, adverse effects, quality control of the data, eligibility of patients, and protocol violations by independent monitoring committees and clinical research associates. Moreover, it will be audited thrice during the trial by a professional company unrelated to the research teams. Safety assessment was performed for all subjects through clinical symptoms and features, which were conducted by telephone interview and clinical examination during a visit to the hospital, and was performed thrice at baseline before drug administration, 14 days after drug administration, and during drug administration. When the patients note undesirable and/or unexpected medical findings, which did not occur prior to the clinical trial, it is defined as an adverse effect; the subject will consult the doctor of the trial committee, and the event will be recorded at any time during the course of the trial. The protocol for this trial was approved by the research ethics committee of the Nara Medical University and was registered with the Japan Registry of Clinical Trials (jRCTs051200160).

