### Secondary Outcomes

The secondary outcomes are listed as follows:

Objective outcome

Total sleep time (TST): time from falling asleep to final awakening (min).Wake time after sleep onset (WASO): total awakening time during sleep (min)Sleep onset latency (SOL): time from bedtime to the initiation of sleep (min).REM sleep/non-REM sleep ratio (%).Deep sleep (N3) time (minutes).Automatically calculated ratio of REM sleep without atonia (RWA) to total REM sleep epochs (%)

Subjective outcome

PDSS-2Pittsburg Sleep QuestionnaireRBDSQ

The sleep index is analyzed using a portable EEG/EOG recording system collected on two consecutive nights within 7 days prior to the intervention and reobtained on one night within 2 days after the 28-day administration of zonisamide, as shown in Figure 2. PDSS-2, Pittsburg sleep questionnaire, and RBDSQ were collected at baseline, 14 days after the administration and 2 days after the 28-day administration. Other clinical evaluation tools such as the Movement Disorder Society (MDS) Unified Parkinson's Disease Rating Scale part 3 and part 4 (32), item “psychosis” and “anxiety” on MDS non-motor rating scale (33), Beck Depression Inventory second edition (34), and Parkinson's Fatigue Scale (35) were performed.

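### The adverse event definition, read literally, leaves out worsening of pre-existing conditions, and the third safety assessment is undated, so adverse events may be under-ascertained

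*Protocol article*

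**What the plan says.** The safety text is in the Intervention section of the protocol article.

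- **Definition.** When "patients note undesirable and/or unexpected medical findings, which did not occur prior to the clinical trial, it is defined as an adverse effect". The subject then consults a trial doctor, and "the event will be recorded at any time during the course of the trial".
- **Mode.** Safety is assessed in all subjects from clinical symptoms and features, "which were conducted by telephone interview and clinical examination during a visit to the hospital".
- **Timing.** The assessment "was performed thrice at baseline before drug administration, 14 days after drug administration, and during drug administration". Subjects in the treatment group "took zonisamide (25 mg per day) before bedtime for 28 days".
- **Oversight.** Independent monitoring committees and clinical research associates monitor adverse effects.

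Three other places bear on this. The exclusion criteria under Participants and Recruitment list "severe dyskinesia, severe mental disease", so milder forms are not barred. Under Secondary Outcomes, the sleep questionnaires "were collected at baseline, 14 days after the administration and 2 days after the 28-day administration". The Statistical Analysis section evaluates adverse event rates between the two groups.

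**The concern.** The definition sets two conditions: the patient notes the finding, and it was absent before the trial. The second is the more serious. Many symptoms relevant to safety in Parkinson's disease are already present before treatment. If one gets worse during the trial, it is not new, and the printed rule does not make it an adverse event. The first condition leaves it unclear whether a finding made by an examiner or shown by a test counts if the patient has not noticed it.

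The timing raises a smaller issue. Three safety assessments are announced, but the third has no date and, as worded, includes the period in which the second falls. The end of the 28 days is not named.

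What is at stake is the safety comparison. Verifying safety is a stated aim in the Abstract and Introduction, and the adverse event rates that serve it depend on this definition.

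**Working it through.** The article gives no adverse event rate, safety power or other figure on this point, so there is nothing to reproduce. The check is mainly of the text.

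**1. Apply the definition to each kind of finding.**
- New, and noted by the patient: counts.
- New, found by an examiner or a test, not noted by the patient: not stated.
- Present before the trial, and worse during it: outside the definition as written.
- Present before the trial, and unchanged: rightly not counted.

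**2. Can patients with pre-existing symptoms enrol?** Yes. The Introduction lists psychosis, hallucinations, depression and cognitive impairment among the conditions behind sleep disorders in this disease, and also names daytime sleepiness and unsteadiness. Entry is open to Hoehn and Yahr stages 1 to 4 with prior levodopa. Dyskinesia and mental disease are excluded only when severe. The Intervention section allows stable antipsychotics and anxiolytics.

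**3. Does other text repair the definition?** No.
- Recording at any time and monitoring by committees both apply to adverse effects as defined. They do not widen the definition.
- Interview and clinical examination can bring findings to light, but the article does not say that such findings count.
- Secondary Outcomes lists motor, psychosis, anxiety, depression and fatigue measures. These cover some of the same domains, but they are not adverse event counts and their timing is not given.

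**4. Timing.** I take the 14 days to run from the first dose, as the parallel questionnaire schedule implies. The last dated safety assessment is then day 14. Dosing days after it: 28 − 14 = 14, and 14/28 = 50%. The undated third assessment could fall anywhere in days 1 to 28.

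**5. Effect on the group comparison.** For each arm, let r be the percentage of patients with at least one event under a full definition, and w the percentage whose only events are ones that the printed definition drops. The recorded rate is r − w, so

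recorded difference = (r_Z − r_P) − (w_Z − w_P),

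with Z for zonisamide and P for placebo. Each recorded rate can only stay the same or fall. The difference shrinks if w_Z > w_P, is unchanged if they are equal, and grows if w_Z < w_P. Two illustrations, with every rate assumed and r_Z = 30%, r_P = 10%:
- w_Z = 15%, w_P = 5%: recorded 15% and 5%, so the difference falls from 20 to 10 points.
- w_Z = w_P = 5%: recorded 25% and 5%, so the difference stays at 20 points.

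The article gives neither r nor w, so it does not determine which case applies.

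**The case against.** The strongest defence has four parts.

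**The patient-noted sentence may be only one route.** It can be read as describing spontaneous reports between visits, alongside active ascertainment by interview and examination. This stands in part. A reader might infer that events count only if the patient notes them, but the article does not say only, and all subjects are interviewed and examined. What remains open is whether findings made there count.

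**The third assessment may be an end-of-treatment contact, badly worded.** Three safety assessments sit beside three questionnaire timepoints, the last of them 2 days after dosing ends. The figure titled as the schedule of examinations is not shown and might settle the matter. This also stands. A reader might infer that the plan has no safety assessment at the end of dosing or that late events are lost. The text supports only that none is explicitly placed there, and events may be recorded at any time.

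**Worsening is measured elsewhere.** The rating scales cover several relevant domains. This limits the loss of information, but it does not bring worsening into the adverse event rates that are compared.

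**A journal article condenses the full protocol.** Grading and reporting windows may reasonably be left to that document. The definition is different, because the article states it, and the stated wording restricts adverse effects to findings that did not occur before the trial.

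**Conclusion.** The point holds as a defect of definition with a lesser defect of timing. As printed, the definition leaves out worsening of pre-existing conditions and does not settle the status of findings made by an examiner or a test. The population includes patients who can have such conditions at entry, and adverse event rates are compared between groups, so adverse events may be under-ascertained. The third safety timepoint is undefined. If the third assessment is not an end-of-treatment one, half of the dosing period could pass without a later scheduled safety assessment.

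A reader might go further and conclude that events are in fact undercounted and that the difference between groups is too small. The article does not support this. It gives no event rates and no share of events that are worsening, and the effect on the difference depends on how that share differs between arms.

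The conclusion rests on a literal reading of the definition and on counting the 14 days from the first dose. It concerns the safety comparison and does not affect the primary outcome, sleep efficiency.

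**What to change.** In the safety paragraph of the Intervention section:

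1. Define an adverse event as any untoward occurrence, or any worsening in severity or frequency of a pre-existing condition, from first dose to final assessment, whether detected by the patient, an examiner or a test.
2. State that worsening is judged against the baseline safety assessment.
3. Give the third safety assessment a date, and reconcile it with the existing contact 2 days after the 28-day administration and with the schedule figure.

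The definition costs only a change of wording, and the baseline safety assessment is already planned. The article does not say how the final contact is made, so the cost of adding a safety assessment there cannot be stated exactly. Telephone interview is already one of the named modes. The downside is that more events will be reported in both arms. Since the trial is single-blind, the criterion for worsening should be set in advance and applied alike to both groups.

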### Primary Outcome

The primary outcome was sleep efficiency (SE), which is the percentage of actual sleep time during sleep (%).

